## Abstract

**Background:**

Improvement in treatment for patients with recurrent ovarian cancer is needed. Standard therapy in patients with platinum-sensitive recurrent ovarian cancer consists of platinum-based chemotherapy. Median overall survival is reported between 18 and 35 months. Currently, the role of surgery in recurrent ovarian cancer is not clear. In selective patients a survival benefit up to 62 months is reported for patients undergoing complete secondary cytoreductive surgery. Whether cytoreductive surgery in recurrent platinum-sensitive ovarian cancer is beneficial remains questionable due to the lack of level I-II evidence.

**Methods/Design:**

Multicentre randomized controlled trial, including all nine gynecologic oncologic centres in the Netherlands and their affiliated hospitals. Eligible patients are women, with first recurrence of FIGO stage Ic-IV platinum-sensitive epithelial ovarian cancer, primary peritoneal cancer or fallopian tube cancer, who meet the inclusion criteria. Participants are randomized between the standard treatment consisting of at least six cycles of intravenous platinum based chemotherapy and the experimental treatment which consists of secondary cytoreductive surgery followed by at least six cycles of intravenous platinum based chemotherapy. Primary outcome measure is progression free survival. In total 230 patients will be randomized. Data will be analysed according to intention to treat.

**Discussion:**

Where the role of cytoreductive surgery is widely accepted in the initial treatment of ovarian cancer, its value in recurrent platinum-sensitive epithelial ovarian cancer has not been established so far. A better understanding of the benefits and patients selection criteria for secondary cytoreductive surgery has to be obtained. Therefore the 4^th^ ovarian cancer consensus conference in 2010 stated that randomized controlled phase 3 trials evaluating the role of surgery in platinum-sensitive recurrent epithelial ovarian cancer are urgently needed. We present a recently started multicentre randomized controlled trial that will investigate the role of secondary cytoreductive surgery followed by chemotherapy will improve progression free survival in selected patients with first recurrence of platinum-sensitive epithelial ovarian cancer.

**Trial registration:**

Netherlands Trial Register number: NTR3337.

## Background

Since overall survival is poor for patients with recurrent platinum-sensitive ovarian cancer, improvement of treatment is needed for these patients. Standard therapy in patients with platinum-sensitive recurrent ovarian cancer is platinum-based chemotherapy [1]. In two large prospective trials this resulted in a median overall survival of 18 and 29 months [2,3]. The recently published OCEANS trial, compared carboplatin in combination with gemcitabine+/- bevacizumab, and reported a median overall survival of 33-35 months [4]. The role of secondary debulking surgery in recurrent ovarian cancer is not clear, and current practice differs widely between institutions. Several studies, nearly all retrospective, with highly selected patients, have demonstrated a survival benefit with survival rates up to 62 months for patients undergoing complete secondary cytoreductive surgery [5]. Three studies evaluated the predictive factors to accomplish complete secondary cytoreductive surgery. The first, the Arbeitsgemeinschaft Gynäkologische Onkologie (AGO) DESKTOP I study, found three predictive factors for complete resection: good performance status, no or small volume of ascites ( <500 ml), and complete primary surgery or FIGO I/II. In these selected patients (AGO-score positive), complete resection was achieved in 79% [6]. The second, the DESKTOP II trial, prospectively validated the AGO score and confirmed a complete resection rate of 76% [7]. However in this validation study only 57% of the score-positive patients underwent a secondary debulking which may have resulted in selection-bias and subsequently reduced validation. The third study of Tian et al. developed a risk model with six predictive factors (FIGO stage, residual tumor after primary surgery, PFI (months), ECOG performance status, CA125 at recurrence (U/ml) and ascites at recurrence) [8]. This model categorizes patients as low or high risk. In the low-risk group the proportion of complete cytoreduction was 53.4% compared with 20.1% in the high-risk group. Inclusion criteria of the current study are based on predictive factors as observed in the mentioned studies. Due to the retrospective nature of most studies reporting on secondary cytoreductive surgery, information on surgery related morbidity and second line chemotherapy is scarce. If secondary cytoreductive surgery causes chemotherapy delays and/or dose reductions, is therefore unknown Bristow et al. reported peri-operative morbidity with a weighted mean of 19.2% [5] which seems comparable to morbidity in primary cytoreductive surgery [9]. Whether cytoreductive surgery in recurrent platinum-sensitive ovarian cancer is really beneficial remains questionable due to the lack of level I-II evidence [10]. Therefore, the 4^th^ ovarian cancer consensus conference in 2010 stated that randomized controlled phase 3 trials that evaluate the role of surgery in platinum-sensitive recurrent ovarian cancer should be considered as a priority [11].

### Objective

The aim of this study is to determine whether secondary cytoreductive surgery followed by platinum-based chemotherapy increases progression-free survival in patients with recurrent platinum sensitive epithelial ovarian cancer, primary peritoneal cancer or fallopian tube cancer.

#### *Primary outcome measure*

Primary outcome measure is progression free survival, defined as the interval between the date of randomisation and the date of progressive disease or death of any cause, whatever occurs first. Progressive disease defined as clinical and radiological signs of recurrence (RECIST 1.1 criteria) [12] or elevated CA 125 (GCIG criteria) and radiological signs of recurrence (RECIST 1.1 criteria) [13].

#### *Secondary outcome measures*

Secondary outcome measures are overall survival, progression free survival since start therapy and after the sixth chemotherapy cycle, quality of life during two years after treatment (EORTC QLQ-C30 version 3.0 and QLQ-OV28, EQ-5D), surgery related morbidity and mortality, toxicity (NCI-CTC Toxicity Scale Version 4.0), tumor response following treatment (RECIST and GCIG criteria).

## Methods/Design

### Study design

This study is a multicenter prospective randomised controlled phase III trial in which all nine Dutch gynaecological oncology centres and affiliated hospitals are participating. Patients with first recurrence of platinum-sensitive epithelial ovarian cancer, primary peritoneal cancer or fallopian tube cancer will be randomly assigned to the control arm and experimental arm in a 1:1 ratio. In the control arm patients receive the standard treatment for platinum-sensitive recurrent ovarian cancer of at least six cycles of intravenous platinum containing chemotherapy. In the experimental arm treatment consists of secondary cytoreductive surgery followed by at least six cycles of intravenous platinum containing chemotherapy (Figure 1).

**Figure 1 F1:**
[figure not shown]
SOCceR trial study design.

### Eligibility criteria

#### *Inclusion criteria patients*

Patients, ≥ 18 years, with first recurrence of platinum-sensitive (≥ 6 months after completion of front-line platinum-taxol chemotherapy) epithelial ovarian cancer, primary peritoneal cancer or fallopian tube cancer, are eligible for this study and can be randomised after given informed consent. First recurrence defined as clinical and radiological signs of recurrence (RECIST 1.1 criteria) or elevated CA 125 (GCIG criteria) and radiological signs of recurrence (RECIST 1.1 criteria).

Inclusion criteria are FIGO stage Ic-IV (FIGO system 1988), first-line treatment consisted of complete or optimal (≤ 1 cm) cytoreductive surgery and (neo-adjuvant) platinum-taxol based chemotherapy, ascites < 500 ml (pocket < 8 cm on ultrasound examination), complete resection seems possible (estimated by a gynaecologic oncologist), good performance status (ECOG 0-1) and administration of platinum based chemotherapy is possible (appropriate laboratory values).

#### *Exclusion criteria patients*

Exclusion criteria are non-epithelial or borderline ovarian tumours, platinum-refractory or resistant tumour, secondary or later recurrence, prior or already planned therapy with respect to recurrence, any disease, medical history or medication not allowing surgery and/or platinum based chemotherapy, concurrent treatment for other primary malignancy except for carcinoma in situ and basal or squamous cell carcinoma of the skin or participation in interfering trial.

### Requirement for participating hospitals

All hospitals can participate in this trial on the condition that chemotherapy in both arms is given by a registered medical oncologist and secondary cytoreductive surgery is performed by a gynaecological oncologist in one of the nine gynaecological oncology centres or one of their affiliated hospitals certified as an ovarian cancer treatment center. In addition, approval by the local Institutional Medical Ethics Committee (MEC) must be settled.

### Patient recruitment

All eligible patients will be evaluated by a multidisciplinary team consisting of at least a gynaecological oncologist, a medical oncologist and an experienced radiologist. Confirmation of recurrent ovarian cancer by cytological or histological investigation is warranted if there is any doubt regarding an abnormal finding on CT-scan. Diagnostic laparoscopy is allowed to estimate whether complete resection is possible and has to be performed by a gynaecological oncologist. All patients who meet the inclusion criteria, will be asked to participate in this study. After obtaining written informed consent, randomisation can take place.

### Randomisation

Randomisation is performed by accessing a central internet-based randomisation programme. Stratification will be done for gynaecologic-oncologic center hospital and completeness of primary cytoreductive surgery (complete vs optimal). Patients will be randomly allocated to both arms in a 1:1 ratio. To ensure patients privacy, patients will be registered by study trial number after randomisation.

### Pre-treatment evaluation

Patients in both treatment arms should be asked to fill out a baseline quality of life questionnaire (EORTC QLQ-C30 version 3.0 and QLQ-OV28, EQ-5D). Furthermore, CA 125 must be determined and a Case Report Form (CRF)with respect to baseline characteristics must be completed.

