### Interventions

#### *Control arm*

Patients in the control arm will receive at least six courses of platinum-containing chemotherapy. The first course should be given as soon as possible but within 4 weeks after randomisation. Chemotherapy dose and schedule, combination with other chemotherapeutic agents and pre-and post-chemotherapy medication and hydration is left to the discretion of the participating center. Before every chemotherapy cycle, hematological, renal, and hepatic function will be determined and toxicity is scored using the common toxicity criteria for adverse effects (CTCAE) version 4.0.

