#### *Experimental arm*

Secondary cytoreductive surgery must be performed within 4 weeks after randomisation. All patients will be prepared for the possibility of a bowel stoma. Surgery is carried out under antibiotic prophylaxis. The combination of antibiotics will be according local standards. The objective of the surgical intervention is complete resection of all visible disease. The extensiveness of surgery is left to the discretion of the gynaecological oncologist. The surgical procedure should start with obtaining a peritoneal fluid sample for cytology. Patients who have at least 500 ml of peritoneal fluid at the time of laparotomy are considered positive for ascites. To gain proper insight in the tumor spread, all adhesions from any previous surgery have to be excised. This is followed by a thorough inspection and palpation of the intra-abdominal and retroperitoneal contents. The extend of tumor growth is carefully recorded in eight abdominal regions. In case of peritonitis the number of tumor deposits will be recorded. Based on this information, a plan for dissection is made. At the end of the cytoreductive procedure, the extensiveness of surgery, duration of the operation, the amount of blood loss and the amount of residual tumor is recorded. Secondary cytoreductive surgery is considered complete if there is no tumor left, optimal if the largest residual tumor is ≤ 1 cm and suboptimal if more than 1 cm residual tumor (diameter (length, width or depth) of the separate tumor depositions) is left. The first chemotherapy course should be given as soon as possible but within 6 weeks after surgery.

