### Data analysis

The results of the study will be analyzed according to the intention to treat principle. All patients will be included in the analysis and patients lost to follow-up will be regarded as censored observations. Progression free and overall survival in both treatment arms will be calculated by the Kaplan-Meier method and compared by using the log-rank test, assuming that the hazard rates in the two treatment arms are roughly proportional over time. If mortality due to surgery is unexpectedly high, resulting in proportional hazard (PH) assumptions that are not valid, the primary comparison of the treatment groups will be based on the one-year progression-free disease rates. In addition, progression free and overall survival since start therapy and after the sixth chemotherapy cycle will be compared.

To adjust for baseline covariates, we will also estimate the treatment effect by Cox’s proportional hazard (PH) regression model, given that the PH assumptions are valid. If the mortality due to surgery is unexpectedly high, resulting in PH assumptions that are not valid, progression free survival since start chemotherapy will be analyzed. At least the following baseline covariates will be considered: completeness of primary surgery, FIGO stage, ECOG performance status, age, disease free interval and CA-125 at recurrence. The significance level of the final primary analysis will be set at 0.0498, and for the interim analysis at 0.001. For all other analyses, 0.05 will be used in the report of study results.

Treatment related morbidity at 30 days after surgery will be analysed with descriptive statistics. Logistic regression will be used to study relations between clinical variables and morbidity. Toxicity after the third and sixth chemotherapy course will be evaluated by means of descriptive statistics and by using an unpaired Student’s t-test or the two-sided Mann-Whitney test for the continuous variables. Comparisons of the proportions of toxicity between the 2 arms will be done by use of a two-sided chi-square test or a two-sided Fisher’s exact test if the number of expected patients in a given category is less than five.

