Quality of life scores will be summarized per time-point, for those subjects, who are alive, once for the original values and once for the changes from baseline. Only subjects who have filled in a baseline questionnaire will be included in the analysis. In addition to descriptive statistics, the Quality Adjusted Life Years (QALY) will be analysed. QALYs will be based on the EQ-5D-3 L questionnaire. The repeated measures indexes will be combined over time using the trapezium rule (area under the Quality Adjusted Life Year curve).

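### The baseline quality-of-life form is not required before allocation, yet completing it decides who enters the quality-of-life analysis

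*Protocol article*

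**What the plan says.** **Order of steps.** Patient recruitment ends with: "After obtaining written informed consent, randomisation can take place". No questionnaire is named as a condition. Randomisation adds that "patients will be registered by study trial number after randomisation". The next section, Pre-treatment evaluation, introduces the form: "Patients in both treatment arms should be asked to fill out a baseline quality of life questionnaire". The instruments are the QLQ-C30, QLQ-OV28 and EQ-5D. The wording for the questionnaire is that patients should be asked; for the CA 125 determination and the baseline CRF in the same paragraph it is must.

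**Time from allocation to treatment.** Control arm: "The first course should be given as soon as possible but within 4 weeks after randomisation". Experimental arm: "Secondary cytoreductive surgery must be performed within 4 weeks after randomisation". No masking is described. Patients allocated to surgery are also prepared for a possible stoma.

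**Analysis.** Data analysis opens with "The results of the study will be analyzed according to the intention to treat principle" and adds that every patient is included. Its quality-of-life paragraph summarises scores in living patients "once for the original values and once for the changes from baseline", and restricts the set: "Only subjects who have filled in a baseline questionnaire will be included in the analysis". QALYs follow from the EQ-5D by the trapezium rule.

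**The concern.** A baseline value serves as a reference only if the allocation cannot have influenced it. Here the form is tied to the start of treatment rather than to randomisation, so a patient may fill it in already knowing whether she faces a laparotomy or chemotherapy alone. Self-reported anxiety, functioning and EQ-5D could respond to that knowledge.

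The exclusion rule adds a second route. If the form can be completed after allocation, whether it is completed can also differ between arms. Removing patients without it then conditions the comparison on an event after randomisation. A patient with every later questionnaire but no baseline form is lost even from the summary of raw scores.

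Quality of life is a secondary endpoint, but it matters to the interpretation. The article uses it to judge the impact of adding surgery, and the sample size section justifies the target gain by the expected surgical morbidity.

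**Working it through.** The plan gives no figure for quality of life, so there is none to reproduce. Its total of 230 patients serves progression-free survival and is used here only for 230/2 = 115 per arm.

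**Step 1: the passages side by side**

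| Question | What the article gives |
|---|---|
| What must precede randomisation? | Eligibility and written consent; no questionnaire (Patient recruitment) |
| Who fills in the baseline form? | Patients described by arm, before treatment (Pre-treatment evaluation) |
| How long may lie between allocation and treatment? | Up to 4 weeks in each arm (Control arm, Experimental arm) |
| Who is in the study analysis? | All patients, by intention to treat (Data analysis) |
| Who is in the quality-of-life analysis? | Only those with a baseline form (Data analysis) |

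The first three rows allow a baseline taken with the arm known, though they do not state it. The last two rows conflict whatever the timing. Timing decides what the conflict costs. If the form comes before allocation, the exclusion loses data equally by design. If the form may come after allocation, the exclusion can be selective by arm.

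**Step 2: effect of a shifted baseline on the change score**

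Change = follow-up − baseline. If knowing the arm moves the mean baseline in one arm by b points and follow-up is untouched, the between-arm difference in change moves by −b. If awaiting surgery lowered scores by b, later change would look b points better for surgery. The summary of raw follow-up scores does not move.

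For scale, the standard error of a two-arm difference in means is SD × √(2/115):
- SD 20 (assumed): 20 × 0.132 = 2.6 points
- SD 22 (assumed): 22 × 0.132 = 2.9 points

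For change scores this is multiplied by √(2(1 − ρ)), where ρ is the within-patient correlation. The factor is 1 if ρ = 0.5 (assumed). All 115 per arm are taken to contribute, so the real standard error would be larger. An assumed shift of 2 to 8 points is then between 2/2.9 = 0.7 and 8/2.6 = about 3 standard errors.

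**Step 3: effect on QALYs**

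Under the trapezium rule the baseline EQ-5D enters only the first interval, with weight (length of interval)/2. With an assumed first interval of 0.5 years and an assumed shift of 0.02 to 0.05:
- 0.02 × 0.5/2 = 0.005 QALY
- 0.05 × 0.5/2 = 0.0125 QALY

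**Step 4: effect of selective completion**

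Assume no true effect, SD 20, and completion correlated r = 0.3 to 0.5 with underlying quality of life. With completion proportion c, the mean among completers is raised by r × SD × φ(z)/c, where z is the normal quantile of c and φ the normal density. The bias is the difference between arms.

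For 95% against 85% at r = 0.3: 0.3 × 20 × (0.2332/0.85 − 0.1031/0.95) = 6 × (0.2743 − 0.1086) = 1.0 point. At r = 0.5 it is 1.7 points.

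| Completion by arm | Analysed | Spurious difference (points) |
|---|---|---|
| 95% v 95% | 109 v 109 | 0 |
| 95% v 90% | 109 v 104 | 0.5 to 0.9 |
| 95% v 85% | 109 v 98 | 1.0 to 1.7 |
| 95% v 75% | 109 v 86 | 1.9 to 3.2 |

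The score SD, r, the completion rates and the size of the shift are all assumptions; the documents give none of them.

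**The case against.** The strongest objection concerns timing. No sentence places the form after randomisation. The reference to both arms may mean only that the form applies to everyone. The baseline CRF stands in the same paragraph, and some baseline facts must be known before allocation: completeness of primary surgery is a stratification factor, and performance status and FIGO stage are eligibility items. The paragraph may thus be a list by topic rather than a visit after allocation. The article condenses a fuller protocol, and its design figure is not shown. This stands as far as it goes: a reader might infer that the form is completed after open randomisation, but the article does not say so. It shows only that completion before allocation is not required.

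Three further points stand in part:
- Raw scores are reported beside change scores and are immune to a shifted baseline. They are not immune to the exclusion.
- The DSMB reviews compliance with the quality-of-life assessments. That may limit missing forms but does not fix when the first is completed.
- The statement that all patients are included runs on into the handling of censored observations, so it may have been written with survival in mind. The intention-to-treat sentence before it covers the results of the study without exception.

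A reader might also infer that intention to treat fails for quality of life because of this form alone. The summaries are already limited to living patients, so that is too strong. Nor do the documents support any particular size of bias. In Step 4, differences in completion of 5 to 10 percentage points give a bias below one standard error.

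**Conclusion.** The point holds in limited form. As written, the article permits a baseline questionnaire completed with the arm known, and it explicitly makes that questionnaire the condition for entering the quality-of-life analysis. Three things can therefore depend on the allocated arm: the change-from-baseline summary, the first interval of the QALY area, and the analysed set. For QALYs the selection applies only if the exclusion is meant to extend to them, which the paragraph leaves open.

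The actual bias is unknown. It is zero if every patient completes the form before learning her arm. Under the assumptions shown it could range from a fraction of a standard error to about 3 standard errors for the change score, and the direction is not known either. Progression-free survival, overall survival and the sample size are untouched, so this is a change that should be made rather than a threat to the primary result.

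The conclusion rests on the article alone. If the full protocol places the form before randomisation, the risk of bias by arm goes, but the unnecessary exclusion and its conflict with the intention-to-treat statement remain.

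**What to change.** 1. State in Patient recruitment and Pre-treatment evaluation that the QLQ-C30, QLQ-OV28 and EQ-5D are completed after consent and before allocation. Have the central randomisation programme ask for confirmation before it releases the arm.
2. Replace the exclusion rule: analyse every randomised patient with any quality-of-life data in the allocated arm, for example with a mixed model that treats baseline as one of the repeated measurements and so tolerates a missing value. State the set used for QALYs and how a missing baseline EQ-5D is handled.
3. For patients already randomised, record the date of the form relative to randomisation, report baseline completion by arm, and give raw-score comparisons at least equal weight with change scores.

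The cost is a change of order at the consent visit, one check in the programme, and a short delay for a patient who has not completed the form. The CA 125 sample and the baseline CRF need not move for this purpose, because the argument concerns self-report by a patient who knows her arm.
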